#### Data collection

##### Socio-demographic questionnaire

This questionnaire includes questions about age, education level, occupation, marital status, living situation, family income sufficiency, type of diabetes, family history of diabetes, and etc.

##### Obstetric history questionnaire

This questionnaire includes questions about the number of pregnancies and childbirths, previous mode of delivery, type of diabetes, previous history of gestational diabetes, preference for infant gender, unintended pregnancy, experience of violence during pregnancy, need for medication treatment, and duration of type 2 diabetes.

##### Maternal and neonatal outcomes checklist

This questionnaire includes questions about preterm birth, cesarean section, neonatal hospitalization in the neonatal intensive care unit.

##### The diabetes management self-efficacy scale

The Diabetes Management Self-Efficacy Scale (DMSES) is a tool used to measure perceived self-efficacy in managing type 2 diabetes. It consists of a 5-point Likert scale with 20 items and four subscales related to nutrition, weight control, medical care, and blood glucose monitoring. The total score ranges from 0 to 200, with higher scores indicating higher self-efficacy for healthy behaviors. The scale has demonstrated good reliability with a Cronbach’s alpha of 0.81 and test-retest reliability of 0.79 [27, 28]. In a recent study, the Arabic version of the scale was validated for women with gestational diabetes, showing good content validity and a Cronbach’s alpha of 0.85 [29].

##### Pregnancy experience scale

The Pregnancy Experience Scale (PES) is a 20-item questionnaire that assesses two domains, “Uplifts” and “Hassles,” during pregnancy. It includes ten items for measuring hassles and ten items for measuring uplifts. Participants rate each item on a four-point Likert scale, with higher scores indicating greater levels of hassles or uplifts experienced during pregnancy [30]. The English version of the PES questionnaire exhibits strong internal consistency, with an overall reliability coefficient of 0.80. Specifically, the “Hassles” domain has a reliability coefficient of 0.82, and the “Uplifts” domain has a reliability coefficient of 0.83. In Iran, the Persian version of the PES questionnaire demonstrates acceptable reliability, with an overall reliability coefficient of 0.71. The “Hassles” domain has a reliability coefficient of 0.77, while the “Uplifts” domain shows good consistency with a reliability coefficient of 0.67 [31].

##### Visual Analog Scale (VAS)

Measuring the level of satisfaction with antenatal care using the Visual Analog Scale (VAS) involves a graded line ruler that is 10 centimeters long. The woman is required to indicate her level of satisfaction on this graded line, with zero representing dissatisfaction and 10 representing the highest level of satisfaction [32].

##### Breastfeeding performance

Breastfeeding performance will be assessed in this study using a questionnaire developed by Agunbiade and Ogunleye, 6 weeks after childbirth. The questionnaire consists of six items, and scoring 4 or higher on the items indicates good breastfeeding performance, based on national guidelines [33].

##### Summary of the diabetes self-care activities questionnaire

The SDSCA is an assessment tool used to measure various aspects of diabetes management. It consists of 11 items that cover areas such as diet, exercise, glucose monitoring, foot care, and smoking. Responses are rated on a scale from 0 to 7 days per week [34]. The tool has shown good internal consistency with high inter-item correlations (0.47) and moderate test-retest reliability (0.40). However, for pregnant women with diabetes, only three areas (diet, exercise, and glucose monitoring) are evaluated because foot care and smoking are not relevant in this context [35].

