#### Specific objectives

The specific objectives of the quantitative phase are as follows:

To compare the mean scores of diabetes self-care activities in weeks 36–39 of pregnancy between the intervention and control groups (receiving Centering Pregnancy group care model and receiving routine care, respectively), while controlling for baseline scores.To compare the mean scores of self-efficacy in weeks 36–39 of pregnancy between the intervention and control groups (receiving Centering Pregnancy group care model and receiving routine care, respectively), while controlling for baseline scores.To compare the mean scores of pregnancy experience in weeks 36–39 of pregnancy between the intervention and control groups (receiving Centering Pregnancy group care model and receiving routine care, respectively), while controlling for baseline scores.

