#### Sample size

The sample size in this study was calculated based on the variable of diabetes self-care activities using the G-Power software. According to the results of the study by Al-Hashmi et al. [26] regarding the variable of diabetes self-care activities, and considering M_1_ = 3.1 and M_2_ = 3.7 (assuming a 25% increase due to intervention), SD_1_ = 1.2 and SD_2_ = 1.2, two-sided α = 0.05, and Power = 90%, the sample size was calculated to be 45 participants. Taking into account a 10% dropout rate, a final sample size of 50 participants in each group was considered.

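### Repeating the self-care questionnaire once inside the 36–39 week window would cheaply recover precision on the outcome the trial is sized on; the single reading is valid and is not the main cause of the low power

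*Protocol article*

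**What the plan says.** All references are to the protocol article.

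- **Sample size.** The self-care score drives the calculation: "The sample size in this study was calculated based on the variable of diabetes self-care activities using the G-Power software". The inputs are "considering M_1_ = 3.1 and M_2_ = 3.7 (assuming a 25% increase due to intervention", with "SD_1_ = 1.2 and SD_2_ = 1.2", and "two-sided α = 0.05, and Power = 90%, the sample size was calculated to be 45 participants". Then: "Taking into account a 10% dropout rate, a final sample size of 50 participants in each group was considered".
- **Specific objectives.** The first objective is "To compare the mean scores of diabetes self-care activities in weeks 36–39 of pregnancy between the intervention and control groups", controlling for baseline. One window is named and no repeat reading is described.
- **Data analysis.** ANCOVA is the planned method for the mean scores.
- **Summary of the diabetes self-care activities questionnaire.** The section describes an 11-item tool and says: "The tool has shown good internal consistency with high inter-item correlations (0.47) and moderate test-retest reliability (0.40". It then says that only diet, exercise and glucose monitoring are evaluated in pregnant women. It gives neither the retest interval nor the population behind the 0.40.
- **Validation of the SDSCA questionnaire.** A test-retest ICC is planned for the translated version, for validation only. Neither the outcome definition nor the sample size uses it.

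**The concern.** A test-retest correlation of 0.40 means that about 60% of the variance of one reading does not reproduce at the next. If the score is taken once, that variation goes straight into the between-arm comparison. Baseline adjustment helps little when the scale tracks itself poorly: at a baseline to follow-up correlation of 0.40, ANCOVA lowers the SD only from 1.20 to 1.10.

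The window spans weeks 36 to 39, so there is room for a second short reading, and averaging two readings is the direct way to reduce variation of this kind. What is at stake is the width of the confidence interval on the sizing outcome, and so the chance of detecting the planned difference of 0.6 without enrolling more women.

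**Working it through.** **Inputs from the article.** Difference 3.7 − 3.1 = 0.6; SD 1.2 in each arm; two-sided α 0.05; 45 analysed per arm (50 less 10% dropout); test-retest 0.40.

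**Assumptions, not in the article.** Baseline to follow-up correlation b = 0.40, with 0.2 as an alternative; correlation r between two readings in the window from 0.40 to 0.8; women treated as independent. Power is for a two-sample t-test (noncentral t).

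**Step 1: the plan's own figure.** The standardised difference is d = 0.6/1.2 = 0.5. Two-sided α 0.05 and 90% power then need 85.03, so 86 per arm, not 45. At 45 per arm the power is 65%. The dropout step is right: 45/0.90 = 50. For ANCOVA to bring about 85 down to 45, 1 − b² must equal 45/85, so b = √(1 − 45/85) ≈ 0.69. That is hard to square with a test-retest figure of 0.40.

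**Step 2: one reading with baseline ANCOVA, b = 0.40.** The residual variance, relative to SD², is 1 − b² = 1 − 0.16 = 0.84. The SD is 1.2 × √0.84 = 1.10, d = 0.6/1.10 = 0.546, and power is 73%.

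**Step 3: mean of two follow-up readings, one baseline.** The relative residual variance is (1 + r)/2 − b². With b = 0.40:

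| r between the two readings | Relative variance | SD | d | Power at 45 per arm |
|---|---|---|---|---|
| one reading only | 0.84 | 1.10 | 0.546 | 73% |
| 0.40 | 0.70 − 0.16 = 0.54 | 0.88 | 0.680 | 89% |
| 0.6 | 0.80 − 0.16 = 0.64 | 0.96 | 0.625 | 83% |
| 0.7 | 0.85 − 0.16 = 0.69 | 1.00 | 0.602 | 81% |
| 0.8 | 0.90 − 0.16 = 0.74 | 1.03 | 0.581 | 78% |

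**Step 4: weaker baseline correlation, b = 0.2.** One reading: 1 − 0.04 = 0.96, power 67%. Two readings: 0.70 − 0.04 = 0.66 at r = 0.40, power 82%; 0.90 − 0.04 = 0.86 at r = 0.8, power 72%.

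**Step 5: early delivery.** Suppose half the women in each arm give only one reading. As an approximation, average the one-reading and two-reading variances, with b = 0.40. At r = 0.40 this is (0.84 + 0.54)/2 = 0.69, power 81%. At r = 0.7 it is (0.84 + 0.69)/2 = 0.765, power 76%.

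**The case against.** The case against is substantial, and most of it limits the point without removing it.

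- **The design is sound as it stands.** One baseline and one follow-up score with ANCOVA is standard and unbiased. The article contradicts nothing here, and a second reading is an efficiency choice. This stands. A condensed article might also omit a repeat reading, but the comparison it states is at one window.
- **A reader might infer that the poor reliability pushes power below plan.** The documents do not support that. The SD of 1.2 enters as the SD of the score and presumably already includes measurement error. The low power comes mainly from the sample size: with 85 per arm, the same single reading gives 90% unadjusted, or 94% with ANCOVA at b = 0.40.
- **A reader might also infer that most of a single reading is noise.** The 0.40 is quoted for the whole tool, while only three areas are used. With no retest interval given, and items that count days in a week, part of the unreproduced 60% may be real change. The share due to error cannot be settled from the article, which is why r is shown as a range.
- **Using 0.40 for both correlations is favourable.** If readings in the window agree better than 0.40, or the baseline correlation is lower, the gain shrinks. It stays positive at every value tried.
- **Averaging leaves some errors untouched.** Participants and outcome assessors are unblinded, and the limitations section concedes social-desirability bias. Stable reporting bias would appear in both readings. Any correlation among women treated in the same group of 2 to 10 also remains.
- **The number of readings depends on time of delivery,** and preterm birth and cesarean section are trial outcomes, so it could differ by arm. This needs a sensitivity analysis.

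**Conclusion.** The point holds as a cheap improvement in precision, not as an error in the design. With 45 analysed per arm and an assumed baseline correlation of 0.40, a second reading adds about 5 to 16 percentage points of power, from 73% to between 78% (r = 0.8) and 89% (r = 0.40). With a baseline correlation of 0.2 the rise is from 67% to between 72% and 82%. If half the women give only one reading, the 73% becomes about 76% to 81% for r from 0.7 to 0.40.

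It does not replace correcting the sample size. The stated inputs need about 86 per arm, and none of the scenarios shown reaches the stated 90% at 45 per arm. The gain also concerns only one of the three primary outcomes. All figures rest on correlations that the article does not supply for this population, and on independence between women.

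**What to change.** 1. In both arms, give the three SDSCA areas used (diet, exercise, glucose monitoring) a second time within weeks 36–39, at least 7 days after the first reading, by the same mode and on the same schedule.
2. Define the SDSCA outcome as the mean of the available readings, with one reading sufficing if the woman delivers first.
3. Add a sensitivity analysis that uses the first reading only, and report the number of readings by arm.
4. Restate the power under Sample size, showing the assumed baseline correlation and the assumed correlation between readings. Correct the 45 per arm at the same time.

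The cost is a protocol amendment and one further questionnaire of at most 11 items per woman, about 100 short contacts. These could be fitted into the interviews and frequent follow-ups already planned under Management of missing data. The burden on participants is slight, and no treatment or care changes.

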#### Validation of the SDSCA questionnaire

The psychometric validation of the SDSCA questionnaire on pregnant women with diabetes in Iran has not been conducted based on the available research. At the outset of the study, written consent will be obtained from the creator of the questionnaire. To establish the validity of the questionnaires, various methods such as translation validity (Forward & Backward Translation), content validity, face validity, and construct validity will be employed.

During the process of translating the questionnaires, the questionnaire items will first be semantically translated from English to Farsi to ensure the preservation of the original version’s concepts and meanings. The initial translations will then undergo review and revision by another translator or a team of reviewers. Subsequently, the merged version will be translated back into the original language, and the final translation will be carried out by a team of translators proficient in both languages. Finally, the translated questionnaire will be reviewed by three to four translators to ensure the accuracy and correctness of the linguistic, semantic, and conceptual aspects of the translation. This meticulous process is implemented to guarantee the precision and accuracy of the questionnaire translation across languages [36].

The face validity of the SDSCA questionnaire will be evaluated using a combination of qualitative and quantitative methods. The qualitative approach aims to identify any ambiguities, inadequacies, or difficulties in understanding the questionnaire items. It also ensures that the items are relevant and appropriate for the intended purpose. Furthermore, the quantitative method known as the impact score will be utilized, with scores above 1.5 considered indicative of acceptable face validity [37].

To assess content validity, a qualitative method will be employed to examine grammar, vocabulary, item importance, placement, and completion time of the questionnaire. Additionally, the quantitative approach involves calculating the Content Validity Ratio (CVR) and the Content Validity Index (CVI) to determine the adequacy and representativeness of the questionnaire’s content.

The construct validity of the tool will be assessed through exploratory factor analysis (EFA) and confirmatory factor analysis (CFA). EFA will help identify underlying factors or dimensions in the data, while CFA will validate the hypothesized factor structure.

The reliability of the tool will be evaluated using the test-retest method, which assesses reproducibility over time. The intra-class correlation (ICC) coefficient will be calculated to determine agreement between repeated administrations. Internal consistency will also be assessed using Cronbach’s alpha coefficient, which measures the coherence and reliability of the tool’s items [38].

##### Sample size required for scale psychometrics

Considering that Nunnally and Bernstein recommend a minimum of 5 samples per item for factor analysis [39], in this study, the sample size based on the 11 items in the SDSCA questionnaire is 55. However, considering that EFA and CFA will be conducted on two separate data sets, 110 participants will be selected.

### Data management

The collected data will be entered into SPSS software version 24 promptly after collection to ensure accuracy. The entries from selected participants will undergo a thorough review to further enhance data accuracy. Regular reminders will be implemented to promote participant adherence and engagement in the study. Informed consent will be obtained, allowing for the use of both electronic and paper records to recover any potentially lost data.

### Management of missing data

To minimize missing data, interviews will be conducted by the research team to complete questionnaires and checklists. Strategies including informed consent, comprehensive follow-up data collection, standardized checklists, and frequent follow-ups will reduce loss to follow-up. In cases of non-adherence or withdrawal, participant outcomes will still be investigated and reported. Missing data will be addressed using multiple imputation, and sensitivity analysis will compare results of modified intention-to-treat analysis with imputed data analysis.

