#### Intervention

The intervention group will participate in an 8-week program consisting of group sessions held every 2 weeks, with each session lasting approximately two hours. These sessions will be led by a midwife who is a PhD student in midwifery and an obstetrician, and the group will consist of 2 to 10 women. The content of each session will be based on the curriculum and materials of the centering pregnancy program, which have been reviewed and approved by the obstetrician and nutritionist.

At the start of each session, the midwife, assisted by the researcher, will conduct measurements of weight, blood pressure, and blood glucose levels using a glucometer. This assessment process will take approximately 30 min. The remaining time, around 60 to 90 min, will be dedicated to group discussions focused on predetermined topics that are relevant to the participants’ needs.

Session 1: The first session will provide diabetes education, covering the risks of diabetes for both the mother and the fetus, the importance of self-monitoring, and nutrition education. This will include introducing food groups, emphasizing the significance of meal control, providing information on food labels, and facilitating discussions on pregnancy-related concerns and coping strategies.Session 2: The second session will continue with diabetes education, focusing on the importance of exercise. Additionally, there will be discussions on pregnancy-related topics such as pain relief during labor and addressing issues of intimate partner violence.Session 3: The third session will address postpartum diabetes and what to expect during the postpartum period. Participants will also receive information on the importance of glucose tolerance testing. Pregnancy-related topics will include discussions on expectations during labor and delivery, as well as contraception.Session 4: The fourth session will emphasize diabetes education related to lifelong health monitoring and the risk of diabetes for offspring. Additionally, there will be discussions on pregnancy-related topics such as newborn care, including sleeping, proper usage of car seats, and feeding (Table 1).

**Table 1 Tab1:** Curriculum for group prenatal care in women with diabetes

Sessions	Pregnancy Titles	Diabetes Titles

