1	Introduction, discussion about expectations from the group, measurement of weight and blood pressure, concerns and normal pregnancy disorders, and coping strategies	Explanation of diabetes risks for mother and fetus and the importance of self-monitoring/introduction of food groups and the importance of meal control/introduction of food labels
2	Introduction, discussion about expectations from the group, measurement of weight and blood pressure, methods of pain relief during childbirth and intimate partner violence	Exercise
3	Introduction, discussion about expectations from the group, measurement of weight and blood pressure, what to expect during labor and delivery, prevention of pregnancy and breastfeeding	Diabetes after pregnancy and postpartum issues, and the importance of glucose tolerance test
4	Introduction, discussion about expectations from the group, measurement of weight and blood pressure, infant care (sleep/car seat/feeding)	Lifelong health monitoring and the risk of developing diabetes for children

The control group will receive standard care based on national guidelines.

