### Strengths and limitations

The present study will be the first of its kind in Iran to implement and evaluate the Centering Pregnancy group care model in pregnant women with diabetes using a mixed methods approach. Other strengths include the use of randomization methods to prevent selection bias in the quantitative phase and the validation of the SDSCA questionnaire, which measures self-care activities, in Iranian women with GDM and pregnant women with type 2 diabetes for the first time. This questionnaire can serve as a standardized and widely used tool for assessing self-care activities in these women in future studies. Furthermore, exploring the experiential understanding of women with diabetes in pregnancy regarding this group care model can provide healthcare professionals with greater knowledge about women’s experiences with diabetes and inform practical interventions for reducing the risk of diabetes in women.

The study has several limitations. Firstly, the reliance on self-report measures, such as the SDSCA questionnaire, may introduce recall bias or social desirability bias. Additionally, there are constraints associated with financial limitations the ability to assess long-term outcomes. Another limitation is the lack of blinding among the providers and participants, which is inherent to the nature of the intervention and could potentially bias the results. However, the statistical analyst will be unaware of the group assignments during the analysis, minimizing this bias. Furthermore, since this type of care is being implemented for the first time in Iran, it relies on the cooperation and acceptance of women, which could lead to attrition bias in the 8-week intervention. Lastly, the generalizability of the study’s findings is limited to women with gestational diabetes and low-risk overt diabetes.

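### The one stated missing-data sensitivity analysis most likely compares two analyses that both assume missing at random, so their agreement says nothing about attrition bias

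*Protocol article*

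**What the plan says.** Four places in the protocol article bear on this.

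- **Management of missing data.** The handling is fixed as "Missing data will be addressed using multiple imputation", and the check on it as "sensitivity analysis will compare results of modified intention-to-treat analysis with imputed data analysis". The modified intention-to-treat set is not defined, no missingness assumption is written down, and no analysis that departs from missing at random is named.
- **The same section, on follow-up.** "In cases of non-adherence or withdrawal, participant outcomes will still be investigated and reported".
- **Strengths and limitations.** Because this type of care is new in Iran, the authors note that "it relies on the cooperation and acceptance of women, which could lead to attrition bias in the 8-week intervention". Under Intervention, only one arm has that programme: "The intervention group will participate in an 8-week program consisting of group sessions held every 2 weeks", whereas "The control group will receive standard care based on national guidelines".
- **Sample size.** "Taking into account a 10% dropout rate, a final sample size of 50 participants in each group was considered". This is the only loss figure given, and it is not split by arm.

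**The concern.** A sensitivity analysis for missing data is useful when it changes the assumption that the data cannot check. Here that assumption is that women with missing outcomes would have scored like women in the same arm with the same baseline score who were measured. Standard multiple imputation makes it, and so does an ANCOVA restricted to women with observed outcomes. If the modified set is the latter, the planned comparison leaves the assumption untouched.

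The protocol itself raises attrition bias linked to acceptance of a programme that one arm receives, and that is where missing at random is least safe. If intervention women with missing outcomes had gained less than those measured, both analyses would be too favourable by about the same amount. Their agreement could then be taken as reassurance on the primary outcomes that it does not provide.

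**Working it through.** **The plan's own figure.** The missing-data section gives no number. The dropout step under Sample size reproduces: 45 / (1 − 0.10) = 50 per group. (The 45 does not follow from its stated inputs: 2 × (1.960 + 1.282)² × 1.2² / 0.6² ≈ 84.1, or 85 per group. That is a separate matter, and nothing below depends on it.)

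**Inputs from the protocol.** 50 per arm; SD 1.2; difference 3.7 − 3.1 = 0.6; dropout 10%; ANCOVA with baseline.

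**Inputs assumed.** The effect of 0.6 applies to women who stay. Intervention women with missing outcomes gain nothing. Control loss is 10% and unrelated to outcome. The baseline–outcome correlation is 0.4 in the first simulation and 0.5 in the second. Imputation uses arm and baseline.

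**Step 1: why the two analyses agree.** When only the outcome is missing, imputed values scatter around the regression line fitted to the observed women. Refitting the same model to observed plus imputed values returns that line on average. The imputation estimate is therefore the available-case ANCOVA estimate plus noise from a finite number of imputations, whatever caused the loss.

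**Step 2: size at the documented loss.** With a share p of intervention outcomes missing and no gain in those women, the effect in all randomised women is (1 − p) × 0.6. At p = 0.10 this is 0.54. Both analyses target 0.60, and 0.60 / 0.54 = 1.11, an overstatement of 0.06 points or about 11%.

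**Step 3: simulation of that scenario.** Two sets of 600 runs with 20 imputations were made. In both, available-case ANCOVA and multiple imputation returned about 0.60 at 10% loss. Across intervention losses of 10%, 20% and 30% the mean absolute gap between them was 0.012 to 0.021. Control-based imputation at 10% loss returned 0.52 in one set and 0.54 in the other, against a target of 0.54.

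**Step 4: a different mechanism.** Here loss in the intervention arm depends on the unobserved outcome, with an assumed strength (3,000 runs, true effect 0.6). It is compared with loss that depends on baseline only.

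| Intervention / control loss | Mechanism | Available-case | Multiple imputation | Mean absolute gap |
|---|---|---|---|---|
| 10% / 10% | baseline only | 0.605 | 0.605 | 0.013 |
| 10% / 10% | outcome-related | 0.710 | 0.710 | 0.012 |
| 30% / 10% (illustrative) | baseline only | 0.604 | 0.604 | 0.021 |
| 30% / 10% (illustrative) | outcome-related | 0.935 | 0.936 | 0.019 |

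The gap is the same size whether the estimates are unbiased or biased, so it cannot distinguish the two situations. With no true effect and 10% outcome-related loss, both analyses averaged 0.119. The available-case test rejected in 9.7% of trials, against 5.1% under baseline-only loss.

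**Step 5: what a delta shift would show.** If intervention women with missing outcomes score δ away from what missing at random predicts, the estimate becomes 0.60 + p × δ. At p = 0.10 and δ = −0.6 that is 0.54, the case in Step 2. Unlike the planned comparison, this moves with the untested assumption.

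**The case against.** The strongest reply is that nothing in the missing-data section is false. Comparing an unimputed with an imputed analysis is a fair check that results do not hinge on the imputation, the text does not claim that it tests informative loss, and a fuller plan that is not shown could add such a test. That stands as far as it goes. But the article does fix a specific sensitivity analysis, the only one it names, and that one is uninformative about the bias the article itself raises.

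Several further objections limit the point.

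- **The shared assumption is inferred.** The modified set is undefined. A version with single imputation would rest on a different assumption. If the set left out women who did not attend, the analysed women would differ and the 0.01 to 0.02 gap would not apply. A reader might infer that non-attenders will be dropped, but the text does not say so. If imputation used extra variables, the estimates could differ, though still within missing at random.
- **The threat is stated as possible.** A reader might infer that the protocol expects loss among women who benefit little, confined to the intervention arm. It says only "which could lead to attrition bias in the 8-week intervention" and mentions neither benefit nor a split by arm. That the programme runs in one arm is documented; the rest is a scenario.
- **Leaving the sessions is not the same as a missing outcome.** Outcomes are to be sought after withdrawal, which lowers the share missing and with it the bias. It does not test the assumption for outcomes that stay missing.
- **The size is modest at 10%.** With 45 per arm the standard error is √(2 × 1.2² / 45) ≈ 0.25, so 0.06 is about a quarter of one standard error. At 20% and 30% loss the same arithmetic gives overstatements of 25% (0.60 / 0.48) and 43% (0.60 / 0.42), but no such loss is documented, so these are illustrations only.

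**Conclusion.** The point holds in a limited form. On the natural reading of the modified set, and with standard imputation from arm and baseline, the stated sensitivity analysis compares two estimates that nearly coincide under any cause of loss. Their agreement is no evidence against attrition bias. At the documented 10% dropout the exposure is about 0.06 SDSCA points, 0.60 reported against 0.54 in all randomised women, if intervention women with missing outcomes gain nothing. Loss more strongly related to outcome would bias both analyses further (about 0.12 at 10% loss in the second simulation), and successful follow-up after withdrawal would shrink the bias.

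A reader might go further and conclude that the trial's result will be biased, or that the main analysis must be replaced. The protocol supports neither: the amount and cause of loss are unknown, and multiple imputation is already the planned handling. This should be corrected because it affects how the primary outcomes are interpreted; it does not undermine the trial.

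**What to change.** 1. State that all randomised women with outcomes, including those who did not attend sessions, are analysed by allocated arm, with multiple imputation for the rest. This removes the ambiguity of the modified set and matches the planned follow-up after withdrawal.
2. Add a sensitivity analysis that departs from missing at random for intervention-arm women with missing primary outcomes: control-based imputation, a delta-adjusted tipping-point analysis, or both. For SDSCA, shifts from 0 to −0.6 would span missing at random to no gain. That grid is one choice among several. At 10% loss it moves the estimate by only 0.06, so it may need to be extended. Report the shift at which the conclusion changes.
3. Keep the modified intention-to-treat comparison as supplementary, with the set defined.

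The cost is a few sentences and a little more analysis on data sets that will be imputed anyway, with no extra data collection. The sensitivity result may look less favourable than the comparison now planned.
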